**Pre-implementation Phase (6 Months Control Period)**				

Baseline, for comparison of SBIR (Screening Brief Intervention, and Referral) effectiveness	Tobacco consumption, alcohol intake, and physical activity levels	Proportion of patients with tobacco consumption, alcohol misuse, and insufficient physical activity levels	Primary data collection from comparison patient group	Paper-based self-administered questionnaire

Pre-implementation (baseline) delivery of SBIR elements by clinical team members.	Providers’ baseline delivery of SBIR elements to patients	Proportion of patients being screened, advised, and referred for each risk factor	Connect Care documentation (electronic health records)	Connect Care data extraction, monthly time points for six months

Baseline	SBIR implementation readiness	Leadership engagement/support, resources for SBIR, providers’ motivation	Primary data collection from providers and organizational leaders	Self-administered questionnaire, interview, and observation

**Implementation Phase (15 Months Intervention Period)**				

Implementation	Providers’ delivery of SBIR to patients: Reach or penetration of SBIR to patients; providers, intervention adherence	Proportion of patients being screened, advised, and referred for each risk factor	Connect Care documentation (electronic health records)	Connect Care data extraction, monthly time points for 15 months

Implementation	Acceptability, appropriateness, and feasibility of SBIR implementation	Proportion of providers being agreed or strongly agreed that SBIR implementation is acceptable, appropriate, and feasible in clinical settings	Primary data collection from providers who implemented SBIR	Survey using a validated tool at six and 12 months of implementation initiated

Implementation	Adherence or adaptation to SBIR implementation and real-world practice change challenges/barriers	Whether providers achieve the goal of screening all patients for the three risk factors and offering brief advice and referral to all eligible patients and if not, why; whether any adaptations were made in implementation, what they were, and why adaptions were made.	Primary data collection from providers who implemented SBIR	Regular conversations/interactions during regular meetings between clinical and research teams using a standardized template.

Implementation	Factors influencing implementation	Unit- and organization-related barriers/facilitators or contextual factors to SBIR implementation	Primary data collection from clinical and administrative leadership (e.g., nurses, unit managers, implementation facilitators)	In-depth interviews at three and nine months after implementation initiated

Patients follow ups: Patients’ experience and perspective	Patient’s knowledge and experience (intervention patient groups)	knowledge about the impacts of the risk factors on health risks and the available services/programs for behavior change; acceptability, perceived stigma, and any challenges with SBIR process or related materials; barriers/facilitators to risk factor-related behavior change.	Primary data collection from patients	Follow up in-depth telephone interviews with a small sample at one months of index hospitalization discharge/visit (recruitment or intervention receive time).

Patient follow ups: Effectiveness of SBIR intervention	Patients’ behavior change status for both control and intervention patient groups	Intention to change behavior, awareness about the problem, commitment to action, uptake to referral programs, active modification of behavior (such as quit attempt, reduce/quit tobacco use, reduce/stop alcohol intake, and initiate/increase physical activity). Covariates for effectiveness outcomes: Sociodemographic/socioeconomic (such as age, sex, marital status, ethnicity, education, employment, income, rurality, immigration-related factors) and overall physical and mental health status.	Primary data collection from patients.	Follow-up telephone interview at six months of index hospitalization discharge/visit. Data collection tool will include the questionnaires guided by the Prochaska model of change process and the risk factor screening questions included in the Connect Care

Healthcare resource use	Hospital readmissions and emergency visits for both control and intervention patient groups	Hospital readmissions and emergency visits during the year after index hospitalization discharge /visit. Reasons/diagnosis for readmissions and emergency visits, and family physician/primary care visits within 1-year of discharge/visit and diagnoses/comorbidities at the time of recruitment to 1-year of index hospitalization discharge/visit.	Administrative health databases: Discharge Abstract Database, National Ambulatory Care Reporting System, and physician claim databases	Data from multiple databases will be accessed through Data and Analytics. and will be linked with the follow-up interviews using the personal health numbers.

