Health care utilization measures include hospital readmissions and emergency visits within one year of the index discharge/visits. These outcomes are of particular importance to facilitate outcome comparisons with other studies as well as because they are important to provide cost-effectiveness assessments to support intervention spread/scale decisions by health system administrators. The health care utilization data will be obtained from linked administrative health databases accessed through the Department of Data and Analytics, the custodian of these routinely collected healthcare data (Table 1).

Data on potential confounding variables including sociodemographic and socioeconomic status for both groups are collected during the 6 months patient follow-up interviews. Diagnosis and comorbidity related variables will be obtained from the administrative health databases. A detailed data collection plan is shown in data collection matrix (Table 1).

*Sample size:* SBIR intervention can increase smoking quit rate at 6-months by 11% [40], reduce alcohol misuse rate at 5-months by 19% [41], and increase patients’ average daily physical activity level by 22% [42]. Based on sample size estimation in relation to tobacco use (with effect size of 11%), we will need a maximum of 1,000 patients in each group (a total sample of 2,000 for controlled and intervention groups) to detect the smallest difference, among all outcomes, between the groups (with a study power of 80% and alpha of 0.05). This is the maximum number needed since tobacco is the least prevalent condition and it will also have the smallest proportion of change in behaviour after intervention, among the three risk factors. We will recruit a total sample of 4,000 (2,000 sample for controlled group and 2,000 for intervention group) to account for the anticipated 50% loss to follow up or nonresponse rate. The expected dropout rate is determined based on our previous paper-based SBIR pilot study [22].

*Analysis:* We will use log-binomial regression models to estimate risk difference and relative risk (for health behaviour change outcomes), and Cox proportional competing risk regression models to estimate hazard rate difference and hazard ratio (for health care use outcomes), to compare outcomes between the two groups adjusting for confounders, such as reasons or diagnosis for visits/admissions, comorbidity, and socioeconomic status.

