## Expected Results and Applicability

Thus far 4 inpatient units and 4 ambulatory clinics in Calgary and Edmonton cities in Alberta have participated in this project. Among those, 1 inpatient unit and 4 ambulatory clinics have completed the 6 months control period and started the implementation of SBIR, and remaining units/clinics are in the 6 months control phase. We have recruited a total of 2015 patients as control research participants (i.e., medium or high-risk level on any of the three risk factors). Of those, 1000 have completed 6 months follow-up calls. A total of 447 patients have received SBIR support from the participating units/clinics, with 175 patients being intervention research participants (i.e., consented for follow up survey). Among those intervention research participants, 48 have completed 1 month follow up survey calls, 75 have completed 6 months follow up calls, and 23 have participated in in-depth qualitative interviews. Approximately 50% of patients are responding to follow-up efforts.

The research participants recruitment and data collection activities are undergoing and key learnings to date are as follows.

High screening uptake: Providers are consistently screening and documenting for the risk factors.Low brief intervention rates: Offering brief advice or engaging patients in conversations about behavior change remains relatively low.Low documentation of brief intervention: When brief interventions are provided, they are often not documented in the Connect Care system.Referral gaps: Referral pathways—particularly for physical activity and alcohol use—are unclear, and referral functionalities for these risk factors are not currently integrated into the Connect Care system.Facilitators of implementation: Implementation is supported by clinical champions, embedded project staff at implementation sites, and ongoing rapid assessment and feedback.Participant eligibility challenges: Many patients are ineligible for the intervention or study participation due to critical health conditions particularly in some high acute care settings. This indicates that careful consideration of the setting and patient acute is important when deciding whether to implement SBIR.Improved recruitment: Using both in-person and phone-call recruitment strategies has led to an increase in participant numbers.

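### As written, the linkage rule and the month-6 collection of socioeconomic confounders would confine the adjusted one-year utilization and cost analyses to patients alive and responding at month 6

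*Protocol article*

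**What the plan says.** The healthcare resource use row of Table 1 (implementation phase) takes readmissions, emergency visits and physician visits from administrative databases and adds that these data "will be linked with the follow-up interviews using the personal health numbers". The row above defines the interview given to both groups: "Follow-up telephone interview at six months of index hospitalization discharge/visit". The 1-month telephone interview in the same table is for a small sample of the intervention group, so the 6-month interview is the natural referent.

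The section on effectiveness outcomes says: "The health care utilization data will be obtained from linked administrative health databases". On confounders it says: "Data on potential confounding variables including sociodemographic and socioeconomic status for both groups are collected during the 6 months patient follow-up interviews", whereas "Diagnosis and comorbidity related variables will be obtained from the administrative health databases". Both the behaviour models and the competing-risk Cox models for utilization are to be fitted "adjusting for confounders, such as reasons or diagnosis for visits/admissions, comorbidity, and socioeconomic status".

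The sample-size paragraph doubles recruitment "to account for the anticipated 50% loss to follow up or nonresponse rate", and the section on expected results reports: "Approximately 50% of patients are responding to follow-up efforts".

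Other text points to everyone enrolled. The section on design and key features follows enrolled research participants for 12 months for both behaviour and utilization data. The effectiveness section counts utilization over the year after recruitment. The post-implementation note in Table 1 gives utilization its own one-year horizon, separate from the six-month horizon for behaviour.

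**The concern.** Readmissions and emergency visits need no patient contact. The only sentence that says what these records are joined to nevertheless names the interview, which about half the participants will not have. A named adjustment variable comes from that same interview, so a complete-case adjusted Cox model would drop non-responders even if their records had been linked.

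Follow-up for these outcomes starts at the index discharge or visit. A cohort entered by answering the telephone about six months later is therefore selected on what happened in the first half of the outcome window. Three things would follow:

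- Deaths in months 0–6 could not occur in the analysed set, although the model is meant to treat death as a competing event.
- If patients with early events respond less often, absolute risk is understated, and with it the utilization cost, because the cost analysis takes its estimates from these models.
- If that tendency differs between the control and intervention periods, a spurious effect enters the hazard ratio and the cost saving.

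About half of the available utilization data would also go unused.

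**Working it through.** **1. The plan's own figure.** 1,000 evaluable per group ÷ (1 − 0.50) = 2,000 per group, 4,000 in total, as stated. Linking from the enrolment list would give up to 4,000 patients for utilization. Linking to completed interviews would give about 4,000 × 0.50 = 2,000.

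**2. Selection within the window.** The documents give no event risk, event timing, mortality or response by event status. The following are assumptions:
- 12-month first-event risk of 40% (also 30% and 50%), with 62% of events in months 0–6;
- 3% dead by month 6, independently of event status;
- 50% of the enrolled responding, i.e. 0.50/0.97 = 0.5155 of survivors;
- an early event multiplies the odds of responding by 0.5, 0.7 or 0.9.

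At 40% risk the early-event share is 0.40 × 0.62 = 0.248, the late-event share is 0.152, and 0.600 have no event. Let p1 and p0 be the response probabilities of survivors with and without an early event. They are solved so that 0.248·p1 + 0.752·p0 = 0.5155 at the given odds ratio. The risk among responders is (0.248·p1 + 0.152·p0)/0.5155.

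| Odds ratio | p1 | p0 | Risk among responders |
|---|---|---|---|
| 0.5 | 0.387 | 0.558 | 35.1% |
| 0.7 | 0.449 | 0.538 | 37.4% |
| 0.9 | 0.496 | 0.522 | 39.2% |

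The true risk of 40% is understated in every row.

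**3. Hazard ratio when the true value is 1.00.** Apparent HR = ln(1 − risk, intervention)/ln(1 − risk, control).
- Odds ratio 0.7 intervention, 0.9 control: 0.469/0.498 = 0.94.
- 0.5 intervention, 0.9 control: 0.432/0.498 = 0.87.
- 0.9 intervention, 0.7 control: 0.498/0.469 = 1.06.
- Equal odds ratios in both groups: 1.00.

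Repeating the unequal cases at 30% and 50% risk gives a range of about 0.86 to 1.07.

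**4. Deaths.** At the assumed 3%, 0.03 × 2,000 = 60 deaths per group by month 6 would be absent from the competing-risk analysis.

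**5. Precision.** Smallest detectable HR at 80% power, two-sided 0.05, 1:1: exp(−2 × (1.96 + 0.84)/√events), with events = patients × assumed risk.

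| Assumed risk | 2,000 patients | 4,000 patients |
|---|---|---|
| 10% | 0.67 | 0.76 |
| 20% | 0.76 | 0.82 |
| 30% | 0.80 | 0.85 |
| 40% | 0.82 | 0.87 |

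At 30% risk, power for HR 0.85 is 51% with 2,000 patients and 80% with 4,000.

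The interim counts (1,000 of 2,015 controls and 75 of 175 intervention participants with a 6-month call) are not used as response rates. The article does not say how many had reached month 6.

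**The case against.** The strongest reply is that no sentence restricts the utilization analysis. A reader might infer that the records are linked to the interviews instead of the enrolment list, and that the analysis is limited to responders. The article says neither. The linkage wording sits in the data-collection column of a matrix and can mean that two sources are merged for everyone enrolled, which fits the 12-month follow-up of enrolled participants. Analysis sets are commonly left to a fuller protocol or SAP, and missing covariates can be imputed. This stands, so the restriction can be called implied but not stated. It does not remove the point, which rests on two things the article does fix: the record linked to, and the time at which a named confounder is collected.

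Two further inferences should not be drawn. The sample-size paragraph speaks of the smallest difference among all outcomes, and a reader might take this to mean that the 50% loss was applied to utilization too. The phrase qualifies the difference to be detected, and the calculation covers only the three risk factors. Likewise, only the intervention group has a 1-month contact, but it reaches only a sample of patients, and nothing shows that it changes month-6 response. It is a possible, unproven source of differential response.

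The hazard-ratio figures also rest wholly on assumed inputs, and the bias vanishes when selection is equal in the two groups.

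**Conclusion.** The point holds as an inconsistency to be resolved. Read literally, the linkage rule and the month-6 covariate collection produce an adjusted utilization and cost analysis of about half the enrolled patients, chosen by a condition met midway through the outcome window. That conflicts with the 12-month follow-up of all enrolled participants.

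The loss of deaths in months 0–6 follows directly from that reading. Understated absolute risk (40% reading as 35.1% to 39.2%) requires that patients with early events respond less. A distorted hazard ratio (about 0.86 to 1.07 when the truth is 1.00) further requires that this selection differ between groups, which the documents neither show nor exclude. For scale, the 0.87 case equals the smallest effect that the full 4,000 could detect at 40% risk. The correction should be made before linkage; it is not evidence that a biased analysis has been done.

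**What to change.** **Table 1, healthcare resource use row.** State that administrative data are linked by personal health number to the enrolment list of all consented participants, with interview data merged where available.

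**Effectiveness section.** State that the utilization and cost analyses include every enrolled participant from the index discharge or visit, that deaths count from that date, and that the 50% loss applies to the interview-based behaviour outcomes.

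**Socioeconomic covariate.** Collect it at enrolment for patients still to be recruited. For non-responders already enrolled, use multiple imputation or administrative or area-level measures. The article reports 2,015 controls but only 175 intervention participants recruited, so new collection at enrolment would reach mainly the intervention group. A measure available alike for both groups would keep the adjustment comparable. Report the interview-completer analysis as a sensitivity analysis.

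**Cost.** A few sentences of text, a linkage request for about 4,000 rather than 2,000 personal health numbers, a check that enrolment consent covers linkage for non-responders, and some imputation work. If the sponsor already intends to link everyone, the edit only removes the ambiguity.

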**Post-implementation (after Intervention Period)**				

Data collection will continue up to one month post-implementation for patient’s knowledge and experience outcomes, up to six months post-implementation for patient’s behavior change outcomes, and up to one-year post-implementation for healthcare resource use outcomes.				

## Research plans for evaluation of intervention effectiveness outcomes

*Study design and participants:* We use a quasi-experimental study design (pre-post with a comparison group). The intervention group are patients from participating units during the SBIR implementation period who screen at increased risk on any of the three risk factors and received brief intervention and referral support. The comparison group are patients from the same units, during a 6-month pre-implementation period, identified as having increased risk on any of the three risk factors, but who do not receive the SBIR intervention.

Study inclusion criteria for the target patient population to be enrolled in the effectiveness study include: Adult patients (>18 years) who are residents of Alberta, have the ability to engage in the SBIR process and data collection, and are attending the participating sites during the study period. Research assistants enroll the eligible patients in the study after they provide informed consent. The patients with severe disease conditions (i.e., unconsciousness and end-stage care) or those with mental or cognitive incapacity are excluded.

*Outcome definition and measurement for both groups:* Key outcomes are patient behaviour change in relation to the modifiable risk factors and health care utilizations in the year after recruitment to the study. Measurement of patient’s behaviour changes involves: questions on patients’ intention to change behaviour, their uptake of referral services (for those who received referrals), and changes in risk level as measured using the same risk factor screening tools used during the SBIR intervention. We also ask patients about tobacco use reduction, tobacco quit attempts, seven- and 30-day tobacco abstinence. The data are being collected via telephone interviews at 6 months follow-up after the index clinic visit, or discharge from a hospital stay, during which the patient was recruited into the study. A sample of participating patients are also called at 1 month after their hospital/clinic visit to ask them about their experience of the SBIR intervention.

Health care utilization measures include hospital readmissions and emergency visits within one year of the index discharge/visits. These outcomes are of particular importance to facilitate outcome comparisons with other studies as well as because they are important to provide cost-effectiveness assessments to support intervention spread/scale decisions by health system administrators. The health care utilization data will be obtained from linked administrative health databases accessed through the Department of Data and Analytics, the custodian of these routinely collected healthcare data (Table 1).

Data on potential confounding variables including sociodemographic and socioeconomic status for both groups are collected during the 6 months patient follow-up interviews. Diagnosis and comorbidity related variables will be obtained from the administrative health databases. A detailed data collection plan is shown in data collection matrix (Table 1).

*Sample size:* SBIR intervention can increase smoking quit rate at 6-months by 11% [40], reduce alcohol misuse rate at 5-months by 19% [41], and increase patients’ average daily physical activity level by 22% [42]. Based on sample size estimation in relation to tobacco use (with effect size of 11%), we will need a maximum of 1,000 patients in each group (a total sample of 2,000 for controlled and intervention groups) to detect the smallest difference, among all outcomes, between the groups (with a study power of 80% and alpha of 0.05). This is the maximum number needed since tobacco is the least prevalent condition and it will also have the smallest proportion of change in behaviour after intervention, among the three risk factors. We will recruit a total sample of 4,000 (2,000 sample for controlled group and 2,000 for intervention group) to account for the anticipated 50% loss to follow up or nonresponse rate. The expected dropout rate is determined based on our previous paper-based SBIR pilot study [22].

*Analysis:* We will use log-binomial regression models to estimate risk difference and relative risk (for health behaviour change outcomes), and Cox proportional competing risk regression models to estimate hazard rate difference and hazard ratio (for health care use outcomes), to compare outcomes between the two groups adjusting for confounders, such as reasons or diagnosis for visits/admissions, comorbidity, and socioeconomic status.

Cost-effectiveness analysis will document the economic value of the SBIR intervention in order to communicate that value to decision-makers. Cost reduction/avoidance within one year, attributable to SBIR, will be estimated based on the reduction in 1-year readmissions and emergency visits, compared to the non-intervention comparison group. Estimates of this economic impact will be provided by applying hospitalization and emergency visit cost data, provided by Canadian Institute of Health Information (CIHI), to the utilization estimates from the above-mentioned models. Intervention implementation cost data are being collected throughout the project.

*Ethical considerations:* This study has received ethics approval from the Health Research Ethics Board of Alberta – Community Health Committee- at the University of Calgary (HREBA.CHC-22-0058).

*Involvement of people with lived experience:* IPiC-Health project has 7 patient advisors, who closely work with the research and innovation team of IPiC-Health project. The patient advisors provide insights based on lived experience to inform SBIR pathways, the research and implementation plan, development of resources, brief conversation scripts, and provide advice on acceptability and appropriateness on all aspects of the research and intervention. The Patients advisors consist of individuals connected to the Alberta Strategy for Patient Oriented Research SUPPORT Unit (AbSPORU) and Patient and Community Engagement Research (PaCER) | University of Calgary-trained patient researchers who have lived experience of care in Alberta’s patient care settings and/or with the risk factors targeted by the SBIR intervention.

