Clinical teams were given flexibility to tailor the implementation process and the timing of brief intervention conversations to best align with patient needs and existing clinical workflows. In acute care settings, for example, these conversations were typically initiated during the later stages of hospitalization, such as in the days leading up to discharge, during discharge preparation, or once patients had passed the most acute phase of their stay. When clinical teams determined that the hospital setting was not appropriate for delivering the intervention to particular patients, providers were empowered to use their clinical judgment to assess the suitability of the intervention. In situations where hospitalized patients were not ready or able to engage with substantial information, patients were given the option to decline the intervention or to receive it during subsequent clinical encounters.

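### Intervention patients are selected on having received SBIR while controls are selected on risk alone, so the effectiveness contrast mixes the SBIR effect with selection into receipt

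*Protocol article*

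**What the plan says.** The section *Research plans for evaluation of intervention effectiveness outcomes* defines the two groups by different rules. Intervention patients are those in participating units during implementation "who screen at increased risk on any of the three risk factors and received brief intervention and referral support". Comparison patients come from the same units in the six months before and are "identified as having increased risk on any of the three risk factors, but who do not receive the SBIR intervention". Consent, ability to take part, and the exclusions for severe illness or incapacity apply to both groups.

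*Expected Results and Applicability* shows the rule in use. For controls: "We have recruited a total of 2015 patients as control research participants (i.e., medium or high-risk level on any of the three risk factors". For the intervention side: "A total of 447 patients have received SBIR support from the participating units/clinics, with 175 patients being intervention research participants".

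*Anticipated implementation challenges and strategies employed* describes how receipt comes about. In acute care, "providers were empowered to use their clinical judgment to assess the suitability of the intervention", and "patients were given the option to decline the intervention or to receive it during subsequent clinical encounters". The progress report adds that screening is consistently done but "Offering brief advice or engaging patients in conversations about behavior change remains relatively low".

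The planned models compare the groups "adjusting for confounders, such as reasons or diagnosis for visits/admissions, comorbidity, and socioeconomic status". Table 1 adds sociodemographic variables and overall physical and mental health. Intention to change appears only as a follow-up outcome.

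**The concern.** An at-risk patient seen during implementation who is not offered SBIR, or who declines it, cannot enter the intervention group. The same kind of patient seen six months earlier can enter the control group. Being offered and accepting the conversation plausibly go with readiness to change, and readiness plausibly predicts quitting, drinking less or becoming more active. A difference between the groups could then arise with no effect of SBIR at all.

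The covariates named are diagnosis, comorbidity, demographic and socioeconomic factors and general health. They do not capture readiness directly. The limitations under *Disadvantage* do not mention this selection.

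The same contrast feeds the health-service-use models and the cost-avoidance estimate for decision-makers. The second project objective concerns the impact of implementing SBIR in these settings, which a comparison of recipients with all enrolled at-risk controls does not estimate.

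**Working it through.** **1. The plan's own figures.** The plan needs 1,000 evaluable per group and expects 50% loss: 1,000 / (1 − 0.50) = 2,000 per group, which reproduces. The 1,000 cannot be verified, because neither the control quit rate nor the scale of the 11% effect is given. If 11% is read as absolute points, with two-sided alpha 0.05 and 80% power, a control quit rate of 11.2% needs 180 smokers per group. If 18% of participants smoke (the article's Alberta population figure), 180 / 0.18 = 1,000. These assumptions are used in step 4.

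**2. Entry conditions side by side.**

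| Condition | Control | Intervention |
|---|---|---|
| Increased risk on any factor | yes | yes |
| Consent and eligibility | yes | yes |
| Judged suitable by provider | no | yes |
| Accepted SBIR | no | yes |
| Received brief intervention and referral | no | yes |

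The last three conditions apply to one group only.

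**3. Size of the bias with zero true effect (all inputs assumed).** Let r be the share of at-risk smokers ready to quit, and let a and b be the probabilities of receiving SBIR if ready and if not ready.

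- Ready share among recipients: s = r·a / [r·a + (1 − r)·b].
- Spurious difference: (s − r) × (quit rate if ready − quit rate if not ready).

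Take r = 30%, with quit rates of 20% if ready and 5% if not. The control rate is 0.30 × 0.20 + 0.70 × 0.05 = 9.5%.

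| Receipt, ready / not ready | s | Recipient quit rate | Spurious difference |
|---|---|---|---|
| equal | 30% | 9.5% | 0 |
| 80% / 40% | 0.24/0.52 = 46.2% | 11.9% | +2.4 points |
| 80% / 20% | 0.24/0.38 = 63.2% | 14.5% | +5.0 points |
| 60% / 10% | 0.18/0.25 = 72.0% | 15.8% | +6.3 points |

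Varying r over 20, 30 and 50% and the ready quit rate over 15, 20 and 30%, with the same three unequal receipt patterns, gives +1.3 to +10.5 points. These are unadjusted and for tobacco only.

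The sign depends on who receives SBIR. If providers reach the less ready more often, say 40% / 80%, then s = 0.12/0.68 = 17.6% and the difference is (0.176 − 0.30) × 0.15 = −1.9 points.

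**4. Price of removing the receipt condition.** If everyone at risk is counted, an 11-point effect in recipients becomes 11 × uptake. Under the assumptions of step 1:

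| Uptake | Effect (points) | Evaluable per group for 80% power | Power with 180 smokers per group |
|---|---|---|---|
| 100% | 11 | 1,000 | 80% |
| 75% | 8.25 | 1,662 | 59% |
| 50% | 5.5 | 3,456 | 32% |
| 25% | 2.75 | 12,673 | 12% |

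**The case against.** The strongest reply is that an effect among recipients is a legitimate question in a hybrid study. Delivery is evaluated separately by interrupted time series, and the *Advantage* section speaks of behaviour change in response to the intervention. That stands as a reason to keep the recipients-only contrast. It does not make the contrast unbiased, because the controls are not the people who would have received SBIR.

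The covariate list is open, and a fuller specification may exist elsewhere. That is fair. However, the article places intention to change at follow-up, and the 2,015 controls are already recruited, so a baseline readiness measure would be hard to add for them.

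Brief interventions are also reported as often undocumented, so actual delivery may be higher than the records show. The strength of the filter is therefore unknown, but that is not evidence that it is absent.

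Four stronger readings are tempting and are not supported:

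- **Controls are every at-risk patient.** They are consenting, eligible patients, and those who later receive SBIR are removed. Some patients whom providers would pass over are thus excluded from both groups.
- **175 of 447 (39%) consenting is a second differential filter.** Consent is required in both groups and no control consent rate is given.
- **Deferred SBIR creates immortal time.** Table 1 and the effectiveness section can be read as starting follow-up at the recruiting encounter, which may be the one where SBIR was delivered. Nothing starts the clock earlier.
- **The bias certainly favours SBIR.** That is the likelier direction, but the documents do not settle it.

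**Conclusion.** The concern holds as a flaw in the stated group definitions. Only the intervention group is conditioned on being offered, accepting and receiving SBIR. The article itself describes receipt as depending on patients and providers, and the named covariates do not include baseline readiness. The resulting estimate cannot be read as the effect of SBIR or of implementing it.

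The documents do not fix the size. Roughly 1 to 10 percentage points is an illustration that rests wholly on assumed readiness, quit rates and receipt probabilities with zero true effect. It shows that the bias could be a material share of the planning effect if the 11% is absolute. It is not an estimate of the bias in this study.

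**What to change.** - **Main contrast.** For the remaining recruitment, enrol consenting patients at the positive risk screen in implementing units, whether or not brief intervention or referral is delivered. Use the same eligibility rules and the same index visit or discharge date as for controls. Make this cohort against the controls the main effectiveness comparison.
- **Secondary contrast.** Keep recipients against controls, propensity-weighted on variables available in both groups, and state selection into receipt as a limitation. The 175 participants enrolled on the receipt rule belong here.
- **Follow-up anchors.** Reconcile the Methods design section (follow-up from receipt of SBIR), Table 1 (index discharge or visit, with recruitment or receipt time in brackets) and the effectiveness section (visit or stay of recruitment).
- **Power.** Restate the 80% power with 1,000 evaluable per group for the main contrast over a plausible range of uptake, giving the control quit rate, the smoking share and the scale of the 11% effect.

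The change in recruitment trigger is feasible: at the reported status 2,000 − 175 = 1,825 intervention participants were still to be enrolled, and screening is reported as consistent. At-risk patients not enrolled at screening cannot be recovered by later analysis. The real cost is dilution. With low delivery, the main contrast could be weakly informative at the planned size, and this should be stated openly alongside the secondary result.
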